##### Parasite density in Cohort 1: secondary and tertiary endpoints

Two analyses will be performed: Total Cohort and ATP Cohort.

The proportion of children with asexual *P. falciparum* parasitaemia in each group at each of the following time points: 6½ months post dose 3 (month 8½) and 19 months post dose 3 (month 21) will be calculated (with 95% CI). The 95% CI on the difference of the proportion between each group will also be calculated.

The geometric mean parasite density in children in each group that are positive for asexual *P. falciparum* parasitaemia, at the following time points: 6½ months post dose 3 (month 8½) and 19 months post dose 3 (month 21) will be calculated (with 95% CI). The 95% CI on the mean difference between each group will be calculated for 7 months post dose 3 (month 8½) and 19 months post dose 3 (month 21).

##### Analysis of haematocrit values in Cohort 1: secondary and tertiary endpoints

For each group, the number and proportion of children with a haematocrit below 25% at month 8½ or month 21 divided by the total number of children for which haematology samples are available at 6½ months post dose 3 (month 8½) or 19 months post dose 3 (month 21) will be calculated with 95% CI. The 95% CI on the difference of the proportion between each group will also be calculated.

##### Cohort 2: secondary endpoint

Time to first infection of asexual stage *P. falciparum* parasites will be examined using Kaplan-Meier curves for both groups and these will be compared using the log-rank test or Wilcoxon test. Cox regression will be used to assess the significance of the group effect and the vaccine efficacy (defined as 1-R, where R is the hazard ratio [RTS,S/AS02A:control vaccine]) will be estimated from the hazard ratio of the RTS,S/AS02A group versus the Control group (with 95% CI) adjusting for prognostic/stratifying factors (see section 10.7.2.2.7).

##### Adjustment for covariates

The risk for malaria infection and development of clinical disease depends on numerous factors related to the parasite, host and vector biology. Estimates of the vaccine efficacy will be made, firstly based on treatment group and secondly adjusted for:

- age: continuous variable.
- bednet use: dichotomous yes/no variable.
- geographical area (“barrios” local government areas): categorical variable.
- distance from health centre (in kilometers): continuous variable.
- IFAT score (anti-parasite antibody levels) at baseline: continuous variable.

An exploratory examination of the marginal effect each of the above covariates have on the treatment estimate may also be undertaken.

To date there has not been any evidence that the pre-vaccination anti-HBs serostatus of subjects impacts on the magnitude of CS response after vaccination with RTS,S/AS02A. However, in the event that anti-HBs serostatus prior to vaccination has an impact on magnitude of CS response then this will be explored as an explanatory variable of vaccine effect.

##### Comparability between study sites

The anti-parasite antibody levels measured by IFAT at screening will be assessed to determine the comparability between study sites in terms of malaria transmission intensity.

##### Exploratory analyses

*Intention-to treat analysis for vaccine efficacy*

***An intention-to-treat analysis will be conducted for all clinical efficacy endpoints incorporating a “time to” analysis (as defined in sections 10.2, 10.3 and Table 4) for the periods of time at risk as defined in section 10.7.2.1. The methodology to be used for this analysis is detailed in section 10.7.2.2.1.***
**(Amended January 17, 2003)**

*Analysis of spleen size*

Mean spleen size (size classified according to the Hackett scale, see section 5.7) will be calculated, with 95% CI, for each group at months 8½and 21. Little background data is available on this indicator of malaria exposure/disease in the study population therefore a descriptive analysis of the variable will be performed.

*~~Intention-to treat analysis for vaccine efficacy~~*

~~An intention-to-treat analysis for the primary efficacy endpoint (see section 10.2 for definition of the primary endpoint) will be prepared. The period of time at risk will be calculated as for the primary efficacy endpoint except that the period will start from first vaccination (day 0) and will last for 8½ months. The same analytical procedures as described in section 10.7.2.2.1 will be used for this analysis.~~ **(Amended January 17, 2003)**

*Analysis of parasite genotyping*

The strain specificity of the vaccine will be examined by calculating vaccine efficacy against time to first infection with the NF54 parasite strain and against time to first infection with all other strains. Confidence intervals will be put around the estimates of efficacy. The two estimates will be descriptive and the trial is not powered to detect a difference in effect.

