### Morbidity in the study area

The population structure is similar to that of many developing countries with 18% of the population under 5 years of age. Mortality in childhood is high; the total mortality rate in children under 5 years of age and infant mortality rates are 173 and 89 per 1000 live births respectively. Malaria is the largest single cause accounting for about a quarter of all deaths. Also important are the other common infectious diseases including acute lower respiratory tract infections (ALRI) and gastroenteritis. Malnutrition is prevalent and is given as the immediate cause of death in about a fifth of all deaths in this age group, although it may be a contributing factor in many more.

Recent data from the Manhiça area have shown that the human immunodeficiency virus 1 (HIV-1) rate in women of child-bearing age is approximately 15% (personal communication from [name]). The rate of maternal to child transmission in Mozambique is unknown but is likely to be similar to other African countries[[13]](#endnote-14). Assuming a rate of 25%, an estimate of about 4% of the children in the study area will be positive for human immunodeficiency virus (HIV).

*Plasmodium falciparum* accounts for 90% of all malaria infections. The prevalence of asexual *P. falciparum* ranges from 13.7%‑21.7% at the end of dry season to 30.5%‑34.0% at the end of rainy season. *P. malariae* is present in all surveys with prevalence ranging between 1.4% and 2.9% while *P. ovale* shows a rather erratic prevalence pattern from survey to survey, ranging from 0% to 6.9%.

The malaria episode rate of children presenting to the hospital (defined as history or documentation of fever associated with any level of parasitaemia) is high. It ranges from 0.13 person years at risk for children aged 1 to 2 years to 0.08 person years at risk for children aged 4 to 5 years.

The prevalence of splenomegaly is 23% in children aged 1-5 years and the prevalence of haematocrit of 25% or less is 2.1% in children aged 1-5 years.

Bednet usage: 10% of households are estimated to use bednets.

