**(Amended January 17, 2003)**

## Detailed description of study stages/visits for Cohort 1

**When materials are provided by GlaxoSmithKline Biologicals, it is mandatory that all clinical samples (including serum samples) be collected using exclusively those materials in the appropriate manner. The use of other materials could result in the exclusion of the subject from analysis. The investigator must ensure that his/her personnel and the laboratory(ies) under his/her supervision comply with this requirement.**

The parents/guardians will be instructed to contact the investigator immediately should the child manifest any signs or symptoms any time throughout the study period that the parents/guardians perceive as serious.

| **Clinic Visit 1: Screening** | | |
| --- | --- | --- |
| **Days *–90 to -7* ~~35 to -7~~: Screening (Amended January 17, 2003)** | | |
| · | | Obtain written/thumb-printed informed consent from the parents/guardians. |
| · | | History taking and physical examination ***– baseline measurement of spleen size, of body weight and height or length, as appropriate for age* (Amended January 17, 2003)** |
| · | | Checking of inclusion/ exclusion criteria. |
| · | | Finger prick blood sample collected (1-2 ml, providing a minimum of 0.5 ml of serum) for baseline analysis of:   - Haematology : Blood Count (BC) which includes platelets, white blood cells, haematocrit and haemoglobin - Biochemistry (creatinine, bilirubin and ALT) - Indirect fluorescent antibody test (IFAT) for anti-parasite antibodies |
| **Clinic Visit 2: First vaccination (Day 0)** | | |
| **Day 0: Pre vaccination 1** | | |
| · | | Provision of photo ID |
| · | | Checking of inclusion/ exclusion criteria. |
| · | | History-related physical examination – pre-vaccination axillary body temperature.~~, baseline measurement of spleen size., body weight~~ ***~~and height or length, as appropriate for age~~* (Amended August 13, 2002) (Amended January 17, 2003)** |
| · | | Randomization |
| · | | Recording of concomitant medication and bednet use for the previous night. |
| · | | Finger prick blood sample collected pre-vaccination (1-2 ml, providing a minimum of 0.5 ml of serum) for baseline analysis of:   - Serology (HBsAg and anti-CS antibodies) |
| · | | Intra-muscular (IM) administration of the first vaccine dose in the deltoid region of the left arm. |

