**(Amended January 17, 2003)**

## Detailed description of study stages/visits for Cohort 2

**When materials are provided by GlaxoSmithKline Biologicals, it is mandatory that all clinical samples (including serum samples) be collected using exclusively those materials in the appropriate manner. The use of other materials could result in the exclusion of the subject from analysis. The investigator must ensure that his/her personnel and the laboratory(ies) under his/her supervision comply with this requirement.**

The parents/guardians will be instructed to contact the investigator immediately should the child manifest any signs or symptoms any time throughout the study period that the parents/guardians perceive as serious.

| **Clinic Visit 1: Screening** | | |
| --- | --- | --- |
| **Days *–90 to* *-7*~~35 to -7~~: Screening (Amended January 17, 2003)** | | |
| · | | Obtain written/thumb-printed informed consent from the parents/guardians. |
| · | | History taking and physical examination - ***baseline measurement of spleen size, body weight and height or length, as appropriate for age* (Amended January 17, 2003)** |
| · | | Checking of inclusion/ exclusion criteria. |
| · | | Finger prick blood sample collected (2 ml, providing a minimum of 1 ml of serum) for baseline analysis of:   - Haematology : Blood Count (BC) which includes platelets, white blood cells, haematocrit and haemoglobin - Biochemistry (creatinine, bilirubin and ALT) - RF1-like antibodies - Indirect fluorescent antibody test (IFAT) for anti-parasite antibodies |
| **Clinic Visit 2: First vaccination (Day 0)** | | |
| **Day 0: Pre vaccination 1** | | |
| · | | Provision of photo ID |
| · | | Checking of inclusion/ exclusion criteria. |
| · | | History-related physical examination – pre-vaccination axillary body temperature, ~~baseline measurement of spleen size, body weight and height or length, as appropriate for age~~**(Amended August 13, 2002) (Amended January 17, 2003)** |
| · | | Randomization |
| · | | Recording of concomitant medication and bednet use for the previous night. |
| · | | Finger prick blood sample collected (1-2 ml, providing a minimum of 0.5 ml of serum) pre-vaccination for baseline analysis of:   - Serology (anti-HBs and anti-CS antibodies and HBsAg) |
| · | | Intra-muscular (IM) administration of the first vaccine dose in the deltoid region of the left arm. |

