## Clinical examination at cross-sectional surveys

All subjects will be examined at the cross-sectional surveys at months 8½ and 21 to determine their body weights, axillary temperatures and spleen sizes, according to Hackett’s method[[31]](#endnote-32) (see Table 3)

Table 3: Classification of spleen sizes according to Hackett

| Class | Description |
| --- | --- |
| 0 | Normal spleen not palpable even on deep inspiration. |
| 1 | Spleen palpable below the costal margin, usually on deep inspiration. |
| 2 | Spleen palpable below the costal margin, but not projected beyond a horizontal line half way between the costal margin and the umbilicus, measured along a line dropped vertically down from the left nipple. |
| 3 | Spleen with lowest palpable point projected more than half way to the umbilicus but not below a line drawn horizontally through it. |
| 4 | Spleen with lowest palpable point projected below the umbilical level but not projected beyond a horizontal line situated half way between the umbilicus and the symphysis pubis. |
| 5 | Spleen with lowest palpable point beyond the lower limit of class 4. |

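### Exploratory spleen size is summarised as a mean of ordinal Hackett classes per group, with no between-group estimate and no use of the screening class

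*Supplement*

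**What the plan says.** Section 10.7.2.2.9 (Exploratory analyses) gives the whole spleen analysis in two sentences. The first fixes the summary: "Mean spleen size (size classified according to the Hackett scale, see section 5.7) will be calculated, with 95% CI, for each group", at months 8½ and 21. The second gives the reason for going no further: "Little background data is available on this indicator of malaria exposure/disease in the study population therefore a descriptive analysis of the variable will be performed".

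The scale is in Table 3 of section 5.7. It has six ordered classes, 0 to 5, defined by anatomical landmarks. Class 0 is "Normal spleen not palpable even on deep inspiration".

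Section 1.1.5 supplies one background figure: "The prevalence of splenomegaly is 23% in children aged 1-5 years".

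Spleen size is also recorded at screening in both cohorts. For Cohort 1, section 5.4 lists "baseline measurement of spleen size, of body weight and height or length, as appropriate for age"; for Cohort 2, section 5.6 lists "baseline measurement of spleen size, body weight and height or length, as appropriate for age". The schedules in sections 5.3 and 5.5 place the measurement under efficacy data collection. Neither the spleen analysis nor the covariate list in section 10.7.2.2.7 uses the screening value.

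Parasite prevalence (section 10.7.2.2.4) and haematocrit below 25% (section 10.7.2.2.5), taken at the same surveys, each get a 95% CI on the difference in proportions between groups.

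**The concern.** Three features of the planned summary weaken it.

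- **The measure.** The steps between Hackett classes have no common unit, so a mean class answers no clear question. It mixes how many children have a palpable spleen with how large those spleens are, and the two can offset each other.
- **No contrast.** In a randomised trial the quantity of interest is the difference between arms. Two separate group intervals are a less sensitive substitute.
- **Unused baseline.** The screening class is the same measurement on the same child before vaccination. It is an obvious adjustment variable that has already been collected.

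The stated reason, limited background data, explains why no hypothesis or sample size was set for spleen. It does not explain leaving out an interval on a difference, which needs no prior data. At stake is the usefulness of an exploratory marker of malaria burden measured three times on each child. No listed endpoint depends on it.

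**Working it through.** **Inputs.** 704 evaluable children per group in Cohort 1, control attack rate 11%, vaccine efficacy 50%, lower limit 15%, 80% power (section 10.6.1). Splenomegaly 23%, ages 1–5 (section 1.1.5). 1:1 allocation (section 3). The documents give no expected vaccine effect on spleen, so the reductions below are assumptions.

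**1. The plan's own sample size.** There is no stated figure for spleen; 704 is the number that would be available. On the log relative risk scale:

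n = [(1−pc)/pc + (1−pt)/pt] × (1.96 + 0.8416)² / [ln((1−VE)/(1−L))]²

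With pc = 0.11 and pt = 0.055 the bracket is 8.091 + 17.182 = 25.273. The squared normal term is 7.849. The denominator is [ln(0.50/0.85)]² = 0.2816. So n = 704.5, against 704 stated. The other six rows of Table 5 also reproduce, and 704/0.9 = 782.2 matches the 782 to be recruited.

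**2. What a mean class can hide.**

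- Arm A: 77% class 0, 23% class 1. Mean = 0.23 × 1 = 0.23.
- Arm B: 88.5% class 0, 11.5% class 2. Mean = 0.115 × 2 = 0.23.

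Prevalence of palpable spleen is 23% against 11.5%, and the means are identical. These distributions are illustrative, as the documents give no class distribution.

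**3. Separate intervals against an interval on the difference.** Take 23% against 18%, n = 704 per group.

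- Control half-width: 1.96 × √(0.23 × 0.77/704) = 3.1 points, so the lower limit is 19.9%.
- Vaccine half-width: 1.96 × √(0.18 × 0.82/704) = 2.8 points, so the upper limit is 20.8%.
- The group intervals overlap.
- Difference: 5.0 ± 1.96 × √[(0.1771 + 0.1476)/704] = 5.0 ± 4.2, that is 0.8 to 9.2 points, which excludes zero.

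**4. Precision and power for the proportion with class 1 or more.** Two-sided 5%, normal approximation, control 23%, 704 per group:

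| Assumed relative reduction | Vaccine arm | CI half-width on difference | Power |
|---|---|---|---|
| 20% | 18.4% | 4.2 points | 57% |
| 25% | 17.25% | 4.2 points | 77% |
| 30% | 16.1% | 4.1 points | 91% |

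The smallest reduction with 80% power is about 26% (23% to 17.0%).

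**5. Sensitivity to the control prevalence.** The relative reduction detectable with 80% power is about 41% at a control prevalence of 10%, 33% at 15%, 26% at 23% and 22% at 30%.

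**The case against.** Much of the case on the other side stands.

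- **Status.** Spleen size is in no list of primary, secondary or tertiary endpoints (sections 10.2 to 10.4), and the plan labels it exploratory and descriptive. Parasitaemia and haematocrit at survey are listed endpoints, so some difference in treatment follows the plan's own hierarchy. This limits the weight of the point. It does not make a mean class the better description.
- **The stated reason.** A reader might infer that section 1.1.5 contradicts the claim of little background data. It does not. One area prevalence, with no class distribution, variance, time trend or expected effect, is compatible with that claim. It is also a figure for ages 1–5 in the area, whereas the trial enrols healthy children aged 1 to 4.
- **Interval coverage.** A reader might infer that a t-type interval fits badly with about 77% of children at zero. Simulation with 704 per group and assumed splits of the palpable classes gave coverage of 94.5% to 94.8% for a nominal 95% interval. The difficulty is meaning, not coverage.
- **Ability to show an effect.** A reader might infer that the planned summary cannot show a vaccine effect. Two independent group means with intervals and known numbers give a crude difference by arithmetic. If the vaccine lowered all palpable classes in proportion, comparing means had simulated power of 60% to 77% for a 25% reduction and 77% to 91% for 30%. What the reported summary cannot supply is baseline adjustment, or protection against the offsetting shown in the working.
- **Other markers.** Splenomegaly is about ten times as common as low haematocrit (section 1.1.5: "the prevalence of haematocrit of 25% or less is 2.1% in children aged 1-5 years"). It might be inferred that the trial therefore lacks a between-arm estimate on any common survey marker. It does not: the same section puts *P. falciparum* prevalence at 13.7% to 21.7% after the dry season and 30.5% to 34.0% after the rains, and survey parasitaemia already gets a CI on the difference.
- **The reporting and analysis plan.** It is not shown and could add detail. But the protocol does not leave the method open here; it names the summary measure and limits the analysis to description.

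**Conclusion.** The point holds as a minor one. The protocol fixes a weaker summary than the data allow: a mean of ordinal classes, reported separately by group, with the screening value unused. Lack of background data is no obstacle to an interval on a difference.

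The gain is a directly interpretable between-arm estimate with a 95% CI of about ±4 points. Power would be about 57%, 77% and 91% for relative reductions of 20%, 25% and 30%. These figures assume control prevalence near 23%, 704 children assessed per group in Cohort 1, and effect sizes that the documents do not supply. Further losses by month 21 would widen the interval. A control prevalence anywhere from 10% to 30% moves the reduction detectable with 80% power from about 41% to about 22%. Any further gain from adjusting for screening class cannot be quantified from the documents.

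The primary conclusion, the sample size and every listed endpoint are unaffected.

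**What to change.** In the reporting and analysis plan, which section 10 requires before the blind is broken, replace the group means as the main summary. At months 8½ and 21:

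1. Tabulate the full Hackett class distribution by arm.
2. Report the proportion with class 1 or more in each arm, with the difference and its 95% CI.
3. Add an exploratory between-arm odds ratio, logistic for class 1 or more or proportional-odds for the full scale, adjusted for screening class and age. Choose the model in advance.
4. State which cohort or cohorts are analysed, since spleen size is measured in both.
5. Keep the analysis labelled exploratory, with no claim attached.

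The cost is a few lines of text and one small model. No new measurement is needed. Fixing the cut-off and model before unblinding also prevents a data-driven choice later.

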### Analysis of safety

All safety and reactogenicity analyses will be performed for the Total Cohort.

The overall percentage of subjects reporting any adverse event after vaccination will be tabulated with exact 95% confidence intervals, by type of adverse event; by severity (any grade, grade 3 only); by relationship (No, Yes, respectively).

The overall percentage of doses for which any adverse event is reported after vaccination will be tabulated with exact 95% confidence intervals, by type of adverse event; by severity (any grade, grade 3 only); by relationship (No, Yes, respectively).

The proportion of subjects with at least one report of unsolicited adverse event, classified by MedRA, reported up to 30 days after vaccination, will be tabulated. The same tabulation will be performed for unsolicited adverse events with relationship to vaccination.

Serious adverse events and discontinuation due to adverse event(s) will be described in detail.

Serum ALT, bilirubin creatinine levels, hematocrit values and body weight that are outside of the reference ranges will be described.

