| N = number of documented doses, n/% = number/percentage of doses followed by a local/general symptom, *axillary body temperature  37.5°C. Grade 3: pain at the injection site; cries when limb is moved/spontaneously painful, swelling; > 20 mm, fever; axillary body temperature  39.0°C; irritability/fussiness; crying that cannot be comforted/prevents normal activity, drowsiness; drowsiness that prevents normal activity, loss of appetite; not eating at all, for other symptoms; adverse event that prevents normal activity. Rel = related to study vaccine. Note: all local symptoms were considered related to study vaccine. | | | | | | | | | | | | | |

As shown in Table 1 and Table 2, pain at the injection site was a frequent symptom across all study groups. In children aged 6-11 years, injection site pain was reported after 88%, 90% and 98% of doses in the 1/5, ½ and full dose RTS,S/AS02A groups respectively, compared to 70%, 90% and 87% in the three control groups. Similarly, in the younger children, pain was experienced after 79%, 84% and 92% of doses in the 1/5, 1/2 and full dose RTS,S/AS02A groups respectively. This compared to 93%, 100% and 100% of subjects in the three control groups. Grade 3 pain was observed more frequently in the RTS,S,S/AS02A groups than controls. In children aged 6-11 years this occurred after 0%, 7%, 13% of doses in the 1/5, ½ and full RTS,S/AS02A groups, but did not occur in the control groups. In the 1-5 year old children, grade 3 pain was experienced after 1%, 6%, 15% of doses across dose levels compared to 0% in the control groups.

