#### Assessment of vaccine reactogenicity

Adverse event data will be collected on ***990*** ~~960~~ recipients of the paediatric dose (0.25 ml dose level) of RTS,S/AS02A in the course of this phase IIb trial in 1-4 year old children. This will allow for the reactogenicity profile of the vaccine to be defined with higher precision than previously done in the smaller paediatric phase I studies (Malaria-015 and Malaria-020).

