  **(Amended January 17, 2003)**
- Enrolment will be performed within 12 weeks.
- Controlled:
- 3 doses of hepatitis B vaccine (Engerix‑B™) to children of ***24*** ~~18~~ months and older.
- 2 doses of a 7-valent pneumococcal conjugate vaccine (Prevnar®, Wyeth Lederle Vaccines) at first and third vaccination and 1 dose of Haemophilus influenzae type b vaccine (Hiberix™) at second vaccination to children less than ***24*** ~~18~~ months. **(Amended January 17, 2003)**
- 3 doses of vaccine (RTS,S/AS02A or control) will be administered using a 0, 1 and 2 month vaccination schedule.
  A full dose (0.5 ml) of the control vaccine or a paediatric dose (0.25 ml dose volume) of the RTS,S/AS02A vaccine will be administered at each vaccination.
- Blinding:
- Vaccination and surveillance period (double-blind phase) from month 0 to the data lock point for primary and secondary objectives (month 8½).
- Single-blind surveillance period (study subjects will remain blinded to treatment allocation until study end as will study staff responsible for endpoint evaluation at health facilities and at cross-sectional surveys) from month 8½ to data lock point for analysis of tertiary objectives (month 21).
- Subjects will be randomly assigned in a 1:1 fashion to receive either the RTS,S/AS02A candidate malaria vaccine or one of the control vaccine regimes. See Section 6.4 for a detailed description of the randomization method.
- Two cohorts will evaluate the effect of the malaria candidate vaccine on clinical malaria disease and malaria infection (Cohorts 1 and 2 respectively, with 1564 subjects in Cohort 1 and ***416*** ~~356~~ subjects in Cohort 2). In Cohort 2 where the efficacy of the vaccine against infection will be evaluated, subjects will receive 4 weeks prior to onset of surveillance one dose of sulfadoxine-pyrimethamine and amodiaquine per day for 3 days, so as to clear any parasitaemia. **(Amended January 17, 2003)**
- Self-contained study, i.e. this study will be independent of other studies.
- Data collection will be by electronic remote data entry (RDE)

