##### Cohort 1: secondary endpoint for estimation of vaccine efficacy given multiple episodes per subject

One of the secondary endpoints is the total number of clinical episodes of symptomatic *P. falciparum* malaria over the time at risk during the 6 month surveillance period (months 2½ to 8½ inclusive) (see section 10.3.1).

The analysis of multiple episodes can be handled within the Cox Model framework available in many commercially-available software packages. The ordinary Cox regression estimate of variance for the coefficients treats each observation as independent. This assumption does not hold when a subject can present multiple episodes. An adjustment to the variance estimate to account for the inter-subject correlation has to be made. This can be achieved by using the jackknife to derive a robust variance estimate for the Cox model[[36]](#endnote-37). This is equivalent to the Lin and Wei sandwich estimator for the Cox model[[37]](#endnote-38). The basic procedure is to fit the ordinary Cox model - initially ignoring the correlation - followed by correcting the naïve variance estimate. This approach can fit within commercially available software.

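### Exact 95% intervals on the pooled per-dose adverse-event percentages ignore that each child contributes up to three doses, so they are somewhat too narrow (minor)

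*Supplement*

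**What the plan says.** Section 10.7.3 (Analysis of safety) plans two parallel summaries of adverse events, each broken down by event type, severity and relationship. The first counts children: "The overall percentage of subjects reporting any adverse event after vaccination will be tabulated with exact 95% confidence intervals". The second counts doses: "The overall percentage of doses for which any adverse event is reported after vaccination will be tabulated with exact 95% confidence intervals". Both use the Total Cohort: "All safety and reactogenicity analyses will be performed for the Total Cohort".

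The Study Design Overview (section 3) fixes the number of doses per child: "3 doses of vaccine (RTS,S/AS02A or control) will be administered using a 0, 1 and 2 month vaccination schedule". No clustered or robust interval is named for the per-dose percentages.

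Section 10.7.2.2.2 deals with the same structure for repeated malaria episodes. It says of the unadjusted analysis: "The ordinary Cox regression estimate of variance for the coefficients treats each observation as independent. This assumption does not hold when a subject can present" more than one episode. It then prescribes a robust variance. Section 10.7.3 has no matching step.

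**The concern.** The child is randomised, but in the per-dose table the dose is the unit of analysis. An exact interval for a percentage is ordinarily the Clopper-Pearson binomial interval, which is valid only for independent observations. A child who has pain, swelling or irritability after one dose may well be more likely to have it after the next, often with the same parent reporting. Under such positive correlation 2970 doses carry less information than 2970 independent observations, and the interval does not have its stated coverage.

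What is at stake is the accuracy of an error bar in a safety table. Reactogenicity is a secondary objective in both cohorts, and this programme reports it per dose: Tables 1 and 2 of the protocol use doses as the denominator.

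**Working it through.** **Inputs**
- Children on RTS,S/AS02A: 990 (section 1.2.2.6).
- Doses per child: 3 (section 3), so at most 990 × 3 = 2970 doses.
- Illustrative per-dose rates, half-dose group, Table 2: any pain 75/89 = 84.3%; any swelling 23/89 = 25.8%; grade 3 swelling 16/89 = 18.0%; grade 3 pain 5/89 = 5.6%. These reproduce the printed percentages.
- Within-child correlation: not in the documents. Assumption: ICC from 0 to 0.5.

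The protocol states no width or precision for the per-dose intervals, so there is no planned figure to reproduce.

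**Step 1: design effect.** With m = 3 doses per child, DE = 1 + (m − 1) × ICC = 1 + 2 × ICC, and the effective number of doses is 2970/DE.

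**Step 2: coverage.** The analytic approximation is 2Φ(1.96/√DE) − 1. As a check, coverage of the Clopper-Pearson interval on 2970 doses was simulated from a beta-binomial model (990 children × 3 doses, 10,000 replicates, true rate 18.0%).

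| ICC | DE | Effective doses | Coverage, analytic | Coverage, simulated |
|---|---|---|---|---|
| 0 | 1.0 | 2970 | 95.0% | 95.3% |
| 0.05 | 1.1 | 2700 | 93.8% | 94.1% |
| 0.1 | 1.2 | 2475 | 92.6% | 93.0% |
| 0.2 | 1.4 | 2121 | 90.2% | 90.3% |
| 0.3 | 1.6 | 1856 | 87.9% | 88.4% |
| 0.5 | 2.0 | 1485 | 83.4% | 83.8% |

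Results at 84.3%, 5.6% and 1% are similar: 88.1%, 88.3% and 89.1% at ICC 0.3. The built-in conservatism of the exact method offsets only an ICC of about 0.02 or less.

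**Step 3: width.** For any swelling at 25.8%, using the normal approximation:
- Unadjusted half-width: 1.96 × √(0.258 × 0.742/2970) = 1.6 points.
- ICC 0.2: 1.57 × √1.4 = 1.9 points (18% wider).
- ICC 0.5: 1.57 × √2.0 = 2.2 points (41% wider).

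For grade 3 swelling at 18.0%, the exact interval on 2970 doses is 16.65% to 19.44%. On the effective number of doses it is 16.28% to 19.82% at ICC 0.3 and 16.08% to 20.05% at ICC 0.5.

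**Step 4: does it distort an informal comparison of arms?** Suppose a reader calls a difference when two equal arms' 95% intervals do not overlap. With no true difference, non-overlap needs a gap of 2 × 1.96 = 3.92 unadjusted single-arm standard errors. The standard error of the difference is √2 × √DE of the same units. So z = 3.92/(√2 × √DE) = 2.77/√DE.
- ICC 0: z = 2.77, two-sided false-positive rate 0.6%.
- ICC 0.2: z = 2.34, 1.9%.
- ICC 0.5: z = 1.96, 5.0%.

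**The case against.** The strongest reply is that little depends on these intervals. Section 10.7.3 plans no between-arm test, difference or threshold. The point estimates do not change. The per-subject table in the same section uses the same breakdowns and is valid. Data Safety Monitoring Board (DSMB) reviews take place after each dose in the first 200 children (section 5.2.4), so each child counts once per review. The ICC is assumed, and at 0.05 coverage is close to nominal. A RAP, not shown here, will follow and could settle the interval method. All of this stands, and it limits the severity.

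A reader might infer two stronger things that the documents do not support.
- **That differences between arms would be declared too easily.** No such comparison is planned, and Step 4 shows that informal comparison by non-overlap stays at or below about 5% false positives up to ICC 0.5.
- **That the precision statement in section 1.2.2.6 is wrong.** It reads: "This will allow for the reactogenicity profile of the vaccine to be defined with higher precision than previously done in the smaller paediatric phase I". It rests on 990 recipients, not on 2970 independent doses. Even at ICC 0.5 there are about 1485 effective doses, against 89 half-dose doses in Table 2.

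The reply does not remove the point itself. The protocol does not leave the interval open: it names one that does not fit pooled doses. Section 10.7.2.2.2 already accepts the principle for repeated episodes.

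**Conclusion.** The point holds, at minor severity. As written, the exact intervals for the pooled per-dose percentages treat a child's repeated doses as independent and under-cover when within-child correlation is positive. Coverage is about 94%, 90% and 84% at ICC 0.05, 0.2 and 0.5. With all 2970 doses pooled, each limit moves by less than about 0.7 point even at ICC 0.5.

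This rests on four assumptions: that exact means binomial, which is the usual reading; that the correlation is positive, which is plausible but not documented; that the ICC range is reasonable; and that all 990 children receive three doses. Missed doses would reduce the design effect. The finding concerns the width of a descriptive interval only. It casts no doubt on the point estimates, the per-subject table or any planned decision.

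**What to change.** In 10.7.3 or the RAP, state that intervals for the percentages pooled over doses treat the child as the cluster, either through a robust (GEE) variance on the logit scale or a bootstrap that resamples children. Keep exact 95% intervals for the per-subject percentages and for dose 1, dose 2 and dose 3 taken separately, where each child counts once.

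The cost is one sentence and a few lines of code, with no new data and no more children. The only downside is slightly wider per-dose intervals.
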